### Hypotheses

We hypothesize the following relationships (Fig 1 shows the tested model):

HP1: higher risk perception, positive outcome expectations and action self-efficacy longitudinally predict the intention to undergo genetic test for BRCA germline mutations.HP2: higher health risk attitude and low intolerance to uncertainty have a longitudinal influence on predicted higher intention, planning and action initiation.HP3: higher intention and coping self-efficacy longitudinally predict higher planning.HP4: higher planning (i.e., action planning, coping planning) and coping self-efficacy longitudinally predict higher action initiation.Based on results by Rauscher et al. [14] and Hallowell and colleagues [50], we formulated a research question: (RQ1) is there any difference between personal outcome expectations and family outcome expectations in their association with intention?HP5: family-referred narrative gain framed message (vs. self-referred narrative gain framed message) will produce greater intention and action to undergo genetic testing for *BRCA 1/2* germline mutations in at-risk men.

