### Statistical analyses

Data exclusion: The answers to the manipulation check will be analyzed before the main analyses to see whether participants have read the message until the end, understood, and recalled the content.

Missing data: presence of missing data will be checked before conducting the main analyses. If a subject does not complete T1 and T2 that subject will be excluded from the analysis.

Normality of the data will be checked before conducting the main analyses. Non-normality will be handled applying either non-parametric tests or SEM with estimator for non-normal distribution.

Statistical analyses will be performed in SPSS version 25 and the *Lavaan* and *SemPaths* packages in RStudio software.

Preliminary analysis: Pearson’s r correlations among variables.

Main analyses: the hypotheses 1, 2, 3, and 4 will be tested either using structural equation modeling (SEM) or multiple regressions. Research question 1 will be tested either using structural equation modeling (SEM) or ANOVA. In case of non-normality in the data, WLSMV will be applied and the Satorra-Bentler scaled test statistic and robust standard errors were used. In the model specification, the factor loading of the first indicator of each latent variable will be set to 1. The following goodness-of-fit indices will be used to evaluate model-data correspondence: the Chi-square value, the Comparative Fit Index (CFI), and the Root Mean Square Error of Approximation (RMSEA). The model will be considered as acceptable when the CFI is higher than .90 and close to .95 and when the RMSEA is .08 or less. Finally, modification indices and the matrix of standardized correlation residuals will be inspected for potential improvement of model fit. Direct, indirect (or mediate), and total effects were also estimated. To test hypothesis number 5 an ANCOVA will be applied.

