**Hypothesis 1.** Predictors will be: risk perception, positive outcome expectations, action self-efficacy. Covariates: demographic, health status. Outcome variable will be: intention to undergo genetic test for BRCA germline mutations.**Hypothesis 2.** Predictors will be: health risk attitude, intolerance to the ambiguity. Covariates: demographic, health status. Outcome variables will be: intention to undergo genetic test for BRCA germline mutations, action and coping planning, action initiation.**Hypothesis 3.** Predictors will be: intention to undergo genetic test for BRCA germline mutations, coping self-efficacy. Covariates: demographic, health status. Outcome variables: action and coping planning.**Hypothesis 4.** Predictors will be: action and coping planning. Covariates: demographic, health status. Outcome variable: action initiation.**Research question 1.** Predictor variable: positive outcome expectations (personal vs family). Outcome: intention to undergo genetic test for BRCA germline mutations.**Hypothesis 5.** Predictor variable: treatment/message (family-referred narrative gain framed message vs. self-referred narrative gain framed message). Outcome variables: intention and action to undergo genetic testing for *BRCA 1/2* germline mutations.

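### If HP3 and HP4 are tested by the listed regressions, two paths leave out traits that HP2 names as influences on both ends, so they are confounded on the plan's own hypotheses

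*Protocol article*

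**What the plan says.** Hypotheses section, HP2: "higher health risk attitude and low intolerance to uncertainty have a longitudinal influence on predicted higher intention, planning and action initiation".

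Statistical analyses, entries by hypothesis:

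- HP2: "Predictors will be: health risk attitude, intolerance to the ambiguity. Covariates: demographic, health status". Its outcomes are intention, action and coping planning, and action initiation.
- HP3: the predictors are intention and "coping self-efficacy. Covariates: demographic, health status. Outcome variables: action and coping planning".
- HP4: "Predictors will be: action and coping planning. Covariates: demographic, health status. Outcome variable: action initiation".

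Method, same section: "the hypotheses 1, 2, 3, and 4 will be tested either using structural equation modeling (SEM) or multiple regressions". No rule says which of the two will be used. SEM is described in some detail (loadings, fit indices, modification indices, direct and indirect effects), and the Hypotheses section refers to a figure showing one tested model.

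Timing: the Time 1 assessment section places both traits before randomisation and message exposure. Intention and planning are collected one to two weeks later, and action during the three months after that.

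**The concern.** A variable that influences both the predictor and the outcome of a path, and precedes both, biases that path unless it is adjusted for. HP2 gives the two traits this role twice: for intention and planning (HP3), and for planning and action (HP4). HP2 also has each trait act in one direction on all three variables, so the spurious association runs the way HP3 and HP4 predict.

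HP3 and HP4 are the volitional half of the HAPA test and serve the secondary objective of explaining intention and action. An intention or planning effect could be reported as a determinant when the two variables only share a trait. The Discussion means the results to inform care providers and policy makers. And because the method is left open, the same hypothesis could be tested adjusted or unadjusted depending on a choice the article does not tie down.

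**Working it through.** **Plan's own figure.** There is none to reproduce. The sample size section concerns an ANCOVA, and the article states no effect sizes for HP1 to HP4. That section gives both 132 and 264 men, so both are used below.

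**Which paths are affected.** A path is confounded on the plan's own terms only if HP2 names a trait effect on both of its ends.

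| Path | Trait effect on predictor stated? | On outcome stated? | Confounded under the listed regression? |
|---|---|---|---|
| HP1: risk perception, outcome expectations, action self-efficacy to intention | No | Yes | Not on HP2 alone |
| HP3: intention to planning | Yes | Yes | Yes |
| HP3: coping self-efficacy to planning | No | Yes | Not on HP2 alone |
| HP4: planning to action | Yes | Yes | Yes |

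**Assumptions for size.** Standardised variables; intolerance of uncertainty reverse-scored so that both traits act in the same direction; each trait has effect a on intention, planning and action; true path zero; two-sided 5% test; seven covariates unrelated to the traits; planning taken as one score.

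**HP3, uncorrelated traits.** The spurious slope is the covariance the traits induce: a² + a² = 2a². Its standard error is about 1/√(N − 10). With z = 2a²·√(N − 10), the rejection rate is P(Z > 1.96 − z) + P(Z < −1.96 − z).

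| a | Slope 2a² | N = 132: z, rate | N = 264: z, rate |
|---|---|---|---|
| .1 | .02 | 0.22, 6% | 0.32, 6% |
| .2 | .08 | 0.88, 14% | 1.27, 25% |
| .3 | .18 | 1.99, 51% | 2.87, 82% |

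Simulation with 2,000 replicates agrees: 15% and 52% at N = 132, and 26% and 82% at N = 264, for a = .2 and .3.

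**HP3, traits correlated r after reverse-scoring.** The slope is a²(2 + 2r). At r = .3 it is 2.6a²: .03, .10 and .23. Simulated rates (1,000 runs per setting, no other covariates) at a = .1, .2 and .3 are about 6%, 23–24% and 78–80% for N = 132, and about 7%, 39–41% and 97–98% for N = 264. A negative r would lower the bias.

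**HP4.** With action treated as continuous, the rates are about the same as for HP3. Action is really yes or no. A logistic model with an assumed uptake of 25% and uncorrelated traits gives 15% at a = .2 and 57% at a = .3 for N = 264. HP4 enters two planning scores. If both depend on the traits and are otherwise unrelated, the spurious effect is shared: on the continuous scale each slope is 2a²/(1 + 2a²), that is .08/1.08 = .07 at a = .2 and .18/1.18 = .15 at a = .3.

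**With the traits in the model.** The HP3 and HP4 estimates return to about zero and rejection to about 4–6%.

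**HP1.** If its predictors are unrelated to the traits, rejection stays at 4–6% even without adjustment. Bias appears only if a correlation is added by assumption.

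**The case against.** The strongest objection is that the article reads as if SEM were intended. It presents one tested model, and most of the Main analyses text concerns SEM. In a joint model the HP2 paths enter the same planning and action equations, so HP3 and HP4 are adjusted; the hypothesis lists would then only say which path tests which hypothesis. This stands for SEM, and it means the paths cannot be called confounded without condition. It does not remove the point, because "will be tested either using structural equation modeling (SEM) or multiple regressions" keeps the regression route open, and the lists are the only statement of what those regressions would contain.

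Two stronger readings are tempting, and the article does not support either.

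- *HP1 is confounded too.* The traits are missing from its list, "Predictors will be: risk perception, positive outcome expectations, action self-efficacy. Covariates: demographic, health status", but HP2 states no trait effect on any HP1 predictor, and a cause of the outcome alone does not confound. The Measures section also files both scales under risk perception, so HP1 may already include them, although the Time 1 section lists them separately.
- *HP4 should also contain intention.* This needs a direct effect of intention on testing. No hypothesis states one, and the HAPA section makes intention a mediator with the volition factors nearest to behaviour. If intention acts only through planning, leaving it out does not bias the planning path.

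It is also fair to say that the size rests on assumed effects and that the objective is secondary and observational. Both stand, and they limit the weight of the point.

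**Conclusion.** The point holds in conditional form. Under the regression option, the intention-to-planning and planning-to-action paths omit two pre-randomisation traits that the plan itself names as influences on both ends. It is a conflict between stated lists and a stated hypothesis, not detail left to a fuller document.

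The effect ranges from negligible at a = .1 to severe at a = .3, assuming a true path of zero and the trait structure set out above. If the traits matter as HP2 expects, the unadjusted tests are unreliable; if they barely matter, adjustment costs almost nothing. A joint SEM that contains the HP2 paths does not have this problem. The primary randomised comparison, HP5, is unaffected. The conclusion does not extend to HP1, to the coping self-efficacy path in HP3, or to the absence of intention from HP4.

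**What to change.** Do one of the following in the Statistical analyses section:

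1. Add the health risk attitude score and the two intolerance-of-uncertainty scores (desire for predictability, uncertainty paralysis) as covariates in the HP3 and HP4 entries; or
2. Replace the either/or wording for HP1 to HP4 with a commitment to one simultaneous model that always contains the HP2 paths to intention, planning and action.

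Also say whether risk perception as an HP1 predictor means only the relative-risk items or includes the two trait scales.

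The cost is wording and about three degrees of freedom per model. The data are already collected at T1, and the planned sample size need not change.

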### Principles of the Health Action Process Approach (HAPA)

According to the Health Action Process Approach [17] there are several variables involved in the implementation of new health behaviors. Specifically, it is possible to identify risk perception, outcome expectancies and action self-efficacy as predisposing factors that have an impact on the informed decision; this is considered the motivation phase, in which subjects begin to form an intention. In this model, the intention to perform a specific health behavior is considered as a middle-level mediator between the variables considered in the motivation phase and those in the volition phase.

Furthermore, according to this model, volition factors involve planning that is further specified as coping and action planning and coping self-efficacy. Volition factors are considered as being influential in the subsequent phase and they are the most proximal predictors to actual behavior decision. This second phase (i.e., the volition phase) should be subdivided in pre-action phase, in which the previous mentioned coping and action planning, and coping self-efficacy take place, and action phase, ending with a behavior.

This model was tested in several health contexts [18, 19], in particular for smoking behavior [17, 20, 21], physical activity [22, 23], dietary [24, 25] and also in cancer-related screening behavior [26]. Those studies demonstrated the efficacy of the theory in explaining the initiation and maintenance of such health preventive behaviors. Together with the principles of the HAPA model, the present study aims to understand whether other psychological factors may explain men’s decision making regarding genetic testing for *BRCA1/2* germline mutations [27]. For this reason, two attitudinal factors are examined: intolerance of uncertainty and health risk attitudes.

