#### Time 2 assessment

The original study protocol approved by the Ethical Committee included a T2 assessment with questions on intention to undergo germline genetic testing and evaluation of the quality of the message content, and a subsequent (3–4 weeks later) T3 with coping self-efficacy, action planning, and coping planning. Since the HAPA model does not state that there should be a waiting time between the measurement of the intention and the coping/action planning, we collapse T2 and T3. Therefore, one-two weeks after the administration of T1, via an online survey, participants reply to questions on intention to undergo germline genetic testing, coping self-efficacy, action planning, and coping planning.

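### The Hypothesis 4 analysis leaves out coping self-efficacy, which HP4 names as a predictor of action initiation

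*Protocol article*

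**What the plan says.** All references are to the protocol article.

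- **Hypotheses, HP4:** "higher planning (i.e., action planning, coping planning) and coping self-efficacy longitudinally predict higher action initiation". That is three measured constructs and one outcome.
- **Statistical analyses, Hypothesis 4:** "Predictors will be: action and coping planning", followed by "Covariates: demographic, health status. Outcome variable: action initiation". Coping self-efficacy is neither a predictor nor a covariate.
- **Hypotheses, HP3:** "higher intention and coping self-efficacy longitudinally predict higher planning". The matching analysis does contain the construct: "Predictors will be: intention to undergo genetic test for BRCA germline mutations, coping self-efficacy". Its outcome there is planning, not action.
- **Principles of the HAPA:** coping self-efficacy is counted among the volition factors, of which the text says that "they are the most proximal predictors to actual behavior decision".
- **Time 2 assessment:** at T2 "participants reply to questions on intention to undergo germline genetic testing, coping self-efficacy, action planning, and coping planning", so the scale is available.
- **Statistical analyses, main analyses:** "the hypotheses 1, 2, 3, and 4 will be tested either using structural equation modeling (SEM) or multiple regressions".

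**The concern.** The article gives a predictor list for each hypothesis, so this is a mismatch between two things that are stated. It is not a detail left to an analysis plan. An analyst who follows the Hypothesis 4 list will report on planning and have no coefficient for coping self-efficacy on action, although HP4 predicts one and the theory section places the construct close to behaviour.

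There is a second, conditional consequence. In the protocol's own model coping self-efficacy leads to planning (HP3) and to action (HP4). If both paths are real, a model of action on planning alone credits planning with part of what belongs to coping self-efficacy. A positive planning result could then appear where planning itself does nothing.

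**Working it through.** **Step 1. Hypotheses against listed analyses, for every analysis with action as an outcome.**

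| Analysis | Predictors listed | Coping self-efficacy included? |
|---|---|---|
| Hypothesis 2 | Health risk attitude, intolerance of ambiguity | No |
| Hypothesis 4 | Action planning, coping planning | No, although HP4 names it |
| Hypothesis 5 | Message group | No |

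Coping self-efficacy appears as a predictor only under Hypothesis 3, where the outcome is planning. The effect of coping self-efficacy on action is therefore in no listed analysis. This step needs no assumption.

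**Step 2. Size of the possible bias.** The protocol states no figure to reproduce, so this is an illustration on standardised variables with a single planning score.

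- a = correlation of coping self-efficacy with planning. Assumed 0.3 to 0.5.
- c = direct effect of coping self-efficacy on action. Assumed 0.1 to 0.3.
- b = true effect of planning on action.

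With coping self-efficacy left out, the apparent planning coefficient is b + a × c, so the bias is a × c:

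- lowest: 0.3 × 0.1 = 0.03
- middle: 0.5 × 0.2 = 0.10
- highest: 0.5 × 0.3 = 0.15

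The bias is upward when both paths are positive, as HP3 and HP4 predict.

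**Step 3. Chance of a significant planning result when b = 0.** Take SE ≈ 1/√N and a two-sided test at 0.05. With z = bias × √N, the chance is Φ(z − 1.96) + Φ(−1.96 − z). The section on sample size gives both 132 and 264, so both are shown.

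| Bias | N = 132 (SE 0.087) | N = 264 (SE 0.062) |
|---|---|---|
| 0.03 | z = 0.34, about 6% | z = 0.49, about 8% |
| 0.10 | z = 1.15, about 21% | z = 1.62, about 37% |
| 0.15 | z = 1.72, about 41% | z = 2.44, about 68% |

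A Fisher z approximation gives nearly the same top values: 40% at N = 132 and 69% at N = 264.

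**Step 4. After the correction.** With coping self-efficacy in the model, the a × c term is removed and the construct gets its own coefficient and test. No figure stated in the protocol changes.

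**The case against.** **SEM may already contain the path.** The article says that Fig 1 shows the tested model, allows SEM for Hypotheses 1 to 4, and plans direct and indirect effects. A single SEM fitted to Fig 1 might include a path from coping self-efficacy to action. The figure was not available, so this can be neither confirmed nor excluded. The objection stands to this extent: the omission is certain under multiple regression and conditional under SEM. Even if the figure has the path, the written list would still disagree with it. Relying on the planned inspection of modification indices to add the path would turn a pre-stated hypothesis into one chosen from the data.

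**It may be a drafting slip.** That is plausible, since the construct is treated as part of the model everywhere else. It makes the correction easier but does not make the list right.

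**Confounding is not established.** A reader might infer that the planning coefficient is confounded as a matter of fact. The documents do not support that. The bias exists only if the HP3 and HP4 paths are true, which is what the study sets out to test. Coping self-efficacy and both planning scales are collected together at T2, so the design does not fix their order.

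**The percentages are rough.** This stands in full. Both inputs are assumed. The formula is linear with one planning variable, whereas Hypothesis 4 has two planning predictors plus covariates and an outcome that is in effect whether a test was taken up. Exclusions for a failed manipulation check or non-completion would lower N further.

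**Conclusion.** The Hypothesis 4 predictor list does not match HP4. One of the three constructs named in HP4 is missing, and no other listed analysis of action supplies it. Under multiple regression the coping self-efficacy part of HP4 goes untested; under SEM the same is true unless Fig 1 adds the path.

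A reader might go further and say that half of HP4 is lost. That is loose, because both planning constructs are still tested.

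The bias of 0.03 to 0.15 SD, and the false-positive rates of roughly 6% to 41% (N = 132) or 8% to 68% (N = 264), depend on the assumed effects and on the HP3 and HP4 paths being true. They show that the omission could matter, not how much it will. The mismatch itself does not rest on them.

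The weight is limited. The section on primary and secondary outcomes makes the message comparison (HP5) primary, and neither that comparison nor the sample size is touched.

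**What to change.** Before data are seen, list the Hypothesis 4 predictors as action planning, coping planning and coping self-efficacy, with the covariates and outcome unchanged. If SEM is used, state that the model includes a direct path from coping self-efficacy to action initiation, and check that Fig 1 and the text agree. If the omission was intended, amend HP4 instead and say why.

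The cost is one model term, or one path. The scale is already collected at T2, so no new data, visit or participants are needed.

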### Primary and secondary outcomes

The primary objective of the present research project is to compare self-referred message to family-referred message promoting men’s adherence to evidence-based guidelines on *BRCA1/2* germline genetic testing. The primary clinical objective is to determine what is the best communication strategy to inform men who are at risk to have a germline mutation because they are relatives of women with such a mutation. The primary hypothesis of the study is that family-referred narrative gain framed message (vs. self-referred narrative gain framed message) will produce greater intention and action to undergo genetic testing for *BRCA 1/2* germline mutations in at-risk men.

The secondary objective is to assess men’s characteristics (demographic information, psychological characteristics, health status) that may explain the intention and the action to undergo genetic test for BRCA germline mutations.

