## Discussion

The present research intends to evaluate what are the psychological determinants of men’s informed decision-making about genetic tests for *BRCA1/2* germline mutation. Another aim is to test two messages, one focused on the self and one on the family, regarding their capability to inform and persuade men. For these purposes, an experimental study with a longitudinal component will be developed.

Men face *BRCA*-related cancer risks as women do and they may also transmit their mutations to their children. Notwithstanding, men have not received much attention for now. They are under-tested compared to women and the communication is not tailored on their needs [58]. This consideration leads to the need to understand how male relatives of women with *BRCA1/2* germline mutations are motivated to protect themselves and others [13].

The results of the present research provide answers related to the immediate impact of several psychological variables, such as risk perception, positive outcome expectations, self-efficacy have on men’s intention, planning, and action initiation. All those variables are included in the HAPA model which is a well-known theory in the field of health psychology explaining motivational, volitional, and behavioral processes leading to health behavior changes [17, 18, 59]. The study will also analyze the role of health risk aversion and intolerance of ambiguity, which are variables linked to decision-making in health domains [31–34, 37, 60]. Finally, the research will inform regarding the effectiveness of two messages tailored on the specific men’s needs and focused one on the self and one on the family.

Data gathered from this study may inform health care providers, policy makers, and public health managers about the psychological variables implicated in the decision-making and the best communication strategies considering the various stages of changes, health risk aversion, and intolerance to the ambiguity. The study will give knowledge on how to modulate messages for the male population aimed at informing their decision-making and will guide genetic counsellors [61] for future interventions.

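### Hypothesis 4 tests planning as a predictor of genetic testing without intention in the model, so any effect of intention that bypasses planning would be credited to planning

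*Protocol article*

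**What the plan says.** All references are to the protocol article.

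- **Statistical analyses.** The Hypothesis 4 line reads "Predictors will be: action and coping planning. Covariates: demographic, health status. Outcome variable: action initiation". The other two listed analyses with action as outcome are Hypothesis 2 (health risk attitude and intolerance of ambiguity) and Hypothesis 5 (message). Intention is a predictor only in Hypothesis 3, where the outcome is planning: "Predictors will be: intention to undergo genetic test for BRCA germline mutations, coping self-efficacy".
- **Hypotheses.** HP3 states that "higher intention and coping self-efficacy longitudinally predict higher planning". HP4 states that "higher planning (i.e., action planning, coping planning) and coping self-efficacy longitudinally predict higher action initiation".
- **Principles of the Health Action Process Approach.** Intention "is considered as a middle-level mediator between the variables considered in the motivation phase and those in the volition phase". Of the volition factors, the article says "they are the most proximal predictors to actual behavior decision".
- **Time 2 assessment.** Intention, coping self-efficacy, action planning and coping planning are all collected in one online survey, one to two weeks after T1.
- **Primary and secondary outcomes.** The primary hypothesis is that the family-referred message "will produce greater intention and action to undergo genetic testing", so intention and action are both outcomes of the message comparison.
- **Statistical analyses, general part.** Hypotheses 1 to 4 may be tested by structural equation modelling (SEM) or by multiple regressions. Preliminary Pearson correlations, direct, indirect and total effects, and inspection of modification indices are also listed.

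**The concern.** By the plan's own account intention drives planning. If intention also affects testing in some other way, it is a measured common cause of planning and action. A man who wants the test may both make plans and book it, without the plans contributing anything. Hypothesis 4 as listed cannot tell that situation from one in which planning matters.

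Two conclusions depend on the distinction. The first is HP4, which could be confirmed when planning adds nothing beyond wanting the test. The second is the reading of a split primary result. If the message moves intention but not testing, one wants to know how strongly intention predicts testing in these men, and no main hypothesis analysis estimates that with planning held fixed. The Discussion also says the results will inform on the impact of psychological variables on men's "intention, planning, and action initiation" and will guide genetic counsellors. A spurious planning effect would misdirect that guidance.

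**Working it through.** The plan states no figure on this point to reproduce. The check has three steps.

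**1. When does leaving intention out matter?** On standardised scales let b be the effect of planning on action, c the direct effect of intention on action (not through planning), and r the intention-planning correlation. The planning coefficient with intention left out is

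b + c × r.

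The document gives none of b, c and r, so all values are assumptions. With b = .20:

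| r | c = 0 | c = .10 | c = .30 |
|---|---|---|---|
| .3 | .20 | .23 | .29 |
| .5 | .20 | .25 | .35 |
| .7 | .20 | .27 | .41 |

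With c = 0, which is full mediation, there is no bias at any r. With c above 0 there is.

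**2. Does the SEM route avoid it?** Not if it contains only the listed paths (intention to planning, planning to action). Take b = 0. Fitted equation by equation, planning receives c × r, and the model-implied total effect of intention is r × (c × r) = c × r². At c = .30 this is .30 × .16 = .05 for r = .4 and .30 × .36 = .11 for r = .6, where the true value is .30. The model would report a mediated effect that does not exist and understate the total.

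**3. How often would planning be declared a predictor?** Binary action was simulated from a probit liability, then analysed by logistic regression on a single planning score with and without intention, two-sided 5% level, 1000 replicates per setting. Assumed: b = 0, r = .4 and .6, c = .3 and .4, uptake 20% and 40%. The two sample sizes are those in the sample size section: 264 planned and 132 calculated.

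| Setting | Planning significant, intention omitted | Planning significant, intention included |
|---|---|---|
| N = 264 | 28 to 87% | about 5% (4 to 6% over all settings) |
| N = 132 | 16 to 58% | about 5% |

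At N = 264 the intention coefficient itself is detected with roughly 80% to over 99% power. With weaker direct effects (r = .5, uptake 30%, N = 264), planning is falsely declared a predictor in about 10% of trials at c = .1 and about 22 to 23% at c = .2.

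**Reverse case, to price the fix.** If planning carries the whole effect (b = .3, c = 0, r = .5, uptake 30%, N = 264), power for planning is about 96% without intention and about 89% with it.

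**The case against.** The strongest reply is that the omission follows the stated theory. Intention is placed before the volition factors, HP3 and HP4 form a chain from intention through planning to action, and no hypothesis posits a direct effect. Under that model the bias is zero, as step 1 confirms. The high rates in step 3 come from reversing the model, with planning inert and intention acting directly. This stands: the harm is conditional, and the Hypothesis 4 line does not contradict HP4 as regards intention. What it does not answer is that full mediation is then assumed and cannot be tested by the listed model.

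A reader might infer that nothing in the plan relates intention to action, or that the trial cannot show whether intention leads to testing. The document does not support that. The preliminary correlations cover the pair, the SEM route gives an indirect effect, and modification indices could reveal a missing direct path. None of these replaces the adjusted estimate, however. Correlations are unadjusted, the indirect effect inherits the problem in step 2, and modification indices are a post hoc search available only if SEM is chosen.

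Nor is intention the sole primary outcome. Action is compared between messages directly, so an intention-only message effect would be visible as such.

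Finally, Fig 1, which shows the tested model, is not available here, and a direct path may be drawn in it. The point therefore rests on the written analysis lines. A separate mismatch in the same line is plain: HP4 names coping self-efficacy as a predictor of action, and the Hypothesis 4 analysis leaves it out. Adding intention would not repair that.

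**Conclusion.** The point holds in a limited form. No main hypothesis analysis enters intention as a predictor of action initiation, and the Hypothesis 4 estimate for planning is protected only by the assumption that intention works entirely through planning. If that assumption is right, nothing is lost. If it is wrong, planning is overstated by c × r, and at N = 264 the false-positive rate ranges from about 10% for a weak direct effect (.1) to 87% at the upper end of the assumed values. All these figures rest on assumed effects, correlation and uptake, on one planning score in place of two, and on no covariates.

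It would go too far to say that planning will take credit for intention's effect, or that the intention result of the message comparison is uninterpretable. The bias is a possibility, and the comparison of messages on intention and on action does not depend on Hypothesis 4. This is a cheap improvement to a secondary analysis and not an error in the primary one.

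**What to change.** In the Hypothesis 4 specification, add T2 intention as a predictor of action initiation beside action planning and coping planning. If SEM is used, include a direct intention-to-action path. State that the planning effect is judged with intention in the model, and report the intention coefficient alongside it. If Fig 1 already shows that path, bring the written analysis line into agreement with it.

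The cost is the wording of one analysis line. Intention is already collected, so there is no added burden on participants. The price is power for planning: about 96% down to 89% in the reverse case above. The fall is larger if planning and intention both act, although part of the apparent power without intention is then the bias itself.
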